## 14.0 Potential Benefits to Participants

### 14.1 Potential Benefits:

Participants may benefit from the study intervention (vitamin C) which may lower SU and gout symptoms. However, most participants (e.g., healthy adults) will not derive any direct benefits from participating in the study. Participants will learn about their laboratory results and other health measures, which may not provide them with significant benefit. In general, the research project has a societal benefit that can potentially improve the management of gout within the Hmong population as well as other populations.

Compensation of up to \$150 USD will be provided for those who completed the study. This compensation is based on the amount of time spent in the study and will be pro-rated for partial completion of each phase at two levels- each associated with provision of a stool sample. Participants will be informed that they can discontinue participation in the study at any time and will be paid for the time they put in.

## 15.0 Statistical Considerations

### 15.1 Data Analysis Plan:

**Genomic Analysis:** We will collaborate with University of Minnesota Genomic Center (UMGC) to extract and purify genomic DNA, genotyping key variants on transporter genes which associated with urate absorption and reuptake, including *ABCG2* and *SLC22A12*.

**Microbiome Analysis:** We will collaborate with UMGC to extract DNA from the stool sample to sequence whole-genome shotgun sequencing of the microbiota. following the UMGC protocol. Whole-genome shotgun sequencing data will be trimmed and processed for quality using SHI7 and strain-level taxa will be annotated by comparison to a public strain database. Microbiome features (alpha diversity, beta diversity, taxon relative abundance, gene functional category) will be analyzed, as described in a previous study.

#### 15.2 Power Analysis:

For an effect size of 0.5 mg/dL SU reduction from baseline by vitamin C, using a one-sided *t*-test, 80% power, type 1 error of 0.01, and 15% drop-out rate, 120 in adults with HU and/or gout (standard deviation, SD of 1.5 mg/dL) and 60 adults without HU and gout (SD of 1 mg/dL) are required.

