## 1.0 Objectives

The objectives of this study include:

- Quantify the impact of vitamin C on patient outcomes, including serum urate level, gout-related symptoms, and obesity (measured by BMI) in both healthy Hmong adults and in Hmong patients with hyperuricemia (HU) and/or gout
- Identify associations between individuals' taxonomic and functional patterns of gut microbiota and its impact on the serum urate lowering effect of vitamin C
- Compare taxonomic and functional patterns of gut microbiota between people with HU and/or gout and people without HU and gout
- Identify associations between individuals' taxonomic and functional patterns of gut microbiota and self-reported acute gout trigger foods

Study design is depicted in **Figure 1**.

[figure not shown]

**Figure 1.** Study Design

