## 2.0 Background

Gout, caused by chronic elevation of serum urate (SU), is the most common form of inflammatory arthritis worldwide. About 3.9% of adults in the U.S. suffer from gout and prevalence is even higher in certain ethnicities. Factors that may influence SU include patients' characteristics (gender, weight, renal function, etc.), genetics, and diet. Foods and beverages that have shown positive association with HU and gout are alcohol (particularly beer), purine-rich foods, red meat, seafood, and sugar-sweetened drinks, while inverse association has been found with dairy intake such as skimmed milk and low-calorie yoghurt, coffee and vitamin C.

The gut microbiota composition and function have been linked to common chronic human disorders, such as obesity, diabetes, non-alcoholic fatty liver disease, and rheumatoid arthritis. Intestinal microbiota of gout patients were also found highly distinct from healthy individuals in both organismal and functional structures from a small study conducted in China. Strategies to use personal microbiome features to predict glucose response to specific food have been proposed. However, **little is known about the impact of microbiota on food and urate-lowering therapy (ULT)**. The translational significance of a microbiota-guided approach to select appropriate foods and medications that could prevent the elevation of SU for individuals with gout or at high risk for gout is significant.

The Hmong are a unique Asian sub-population. Hmong men exhibit a 2-fold higher prevalence of gout, manifesting it earlier in life and experiencing up to 5-fold increased risk of gout-associated complications, compared to non-Hmong in the US. This could lead to higher rates of cardiometabolic diseases (e.g. hypertension, renal disease, type 2 diabetes [T2DM]), which significantly impact morbidity, mortality and healthcare costs. To prevent acute gout attack and reduce complications associated with gout and/or HU, it is critical to maintain UA below 6 mg/dL.

In this study, we will test four hypotheses and thereby accomplish our objectives as following:

**Ho (1):** High dose vitamin C intervention improves outcomes in (a) healthy adults and (b) patients with HU and/or gout.

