Rationale: Previous studies had demonstrated vitamin C 500 mg twice daily for 8 weeks is effective in lowering serum urate compared to placebo in healthy adults. However, one study in patients with gout receiving vitamin 500 mg once daily for 8 weeks did not find significant serum urate reduction in patients on allopurinol.

We will test this Ho1 (a) and (b) by giving vitamin C 500 mg twice daily to all the study participants and analyze by 3 groups: 1) participants with HU and/or gout with ULT, 2) participants with HU and/or gout without ULT, and 3) participants without HU and gout.

The outcome measures include both biological surrogate marker (serum urate), patient reported outcome (gout-related symptoms), and obesity (measured by BMI).

**Ho (2):** The urate-lowering effect by vitamin C is influenced by gut microbiome.

Rationale: Humans cannot produce their own vitamin C; therefore, dietary is an important source of vitamin C. However, recent computational analysis identified *Burkholderia*, *Pseudomonas* and *Erwinia* possessed the machinery to produce ascorbate. These genera are commonly seen in patients with Crohn's disease. The presence of these organisms can impact the production of the anti-inflammatory ascorbate metabolite. This could have an impact on the treatment effect (most likely the anti-inflammatory effect) of vitamin C in patients with gout.

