### **4.0 Study Intervention(s)/Investigational Agent(s)**

4.1 Description:

All participants will be taking vitamin C 500 mg twice daily by mouth for 8 weeks. All participants will continue taking their prescribed medications during the study period.

Vitamin C is commercially available over-the-counter food supplements. Vitamin C will be purchased from a GMP manufacturer (such as Pure Encapsulations, Sudbury, MA) which can demonstrate a good quality and safety of the product.

4.2 Drug/Device Handling:

The vitamin C will be stored securely in a locked cabinet at [name] office. Vitamin C is an over-the-counter product and will be distributed by research staff as per applicable regulations. The label will list the name of the study, the number and frequency of tablets to be taken, the participant's name and ID number, and the phone number for a pharmacy helpline. A study dispensing and accountability log will be maintained by bilingual research staff. The participants will be reminded to return the study pill containers and any remaining tablets at Week 8.

- 4.3 Biosafety: This study does NOT involve recombinant or synthetic nucleic acid molecules (r/sNA; RNA, DNA), infectious agents, or biologically-derived toxins.
- 4.4 Stem Cells: This study does NOT involve embryos or embryonic stem cells.
- 4.5 Fetal Tissue: This study does NOT involve human fetal tissue or cell lines derived from human fetal tissue.

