## 5.0 Procedures Involved

- 5.1 Study Design: This is an open-label interventional study. We aim to enroll 2:1 matching between participants with HU and/ or gout and participants without HU and gout. We aim to have 3 analysis groups of about 60 people per group (total about 180 participants): 1) people with HU or gout with ULT, 2) people with HU or gout without ULT, 3) people without HU or gout without ULT.

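### Objective 1 and Ho1 claim an effect of vitamin C, but the only planned urate test is an uncontrolled change from baseline, powered on an effect the protocol describes as placebo-compared

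*Protocol*

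**What the plan says.** Section 1.0 sets the first objective as "Quantify the impact of vitamin C on patient outcomes", naming serum urate, gout symptoms and BMI. Section 2.0 states Ho1 as "High dose vitamin C intervention improves outcomes in (a) healthy adults and (b) patients with HU and/or gout". Both are causal statements.

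The design has no untreated comparator. Section 4.1: "All participants will be taking vitamin C 500 mg twice daily by mouth for 8 weeks". Section 5.1: "This is an open-label interventional study". Ho1 is to be tested by "giving vitamin C 500 mg twice daily to all the study participants and analyze by 3 groups". Those groups are defined by disease and urate-lowering therapy (ULT), so the group without hyperuricemia (HU) or gout is treated too.

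The primary endpoint (Section 3.1) is absolute change in serum urate after 8 weeks. Section 15.3 analyses that change by linear regression on patient characteristics, with no control term.

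Section 15.2 sizes the study "For an effect size of 0.5 mg/dL SU reduction from baseline by vitamin C", citing reference 14. The rationale for Ho1 cites the same reference for the statement that vitamin C "is effective in lowering serum urate compared to placebo in healthy adults". In the reference list, its title calls it a meta-analysis of randomized controlled trials.

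**The concern.** Ho1 concerns what vitamin C does. The test's null hypothesis is that mean urate at week 8 equals mean urate at baseline. These are the same question only if urate would have stayed flat over the 8 weeks without vitamin C. A placebo-compared trial needs no such assumption, because the placebo arm supplies the untreated change. This trial does need it and does not say so.

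Section 15.2 makes the gap harder to see. It presents as a fall from baseline a figure whose source the protocol itself describes as placebo-compared. At stake is what a significant result means: the design supports the statement that urate changed while people took vitamin C. It does not support, at a 0.01 error rate, the statement that vitamin C changed it.

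**Working it through.** **Inputs.** Section 15.2 gives an effect of 0.5 mg/dL, a one-sided t-test, type 1 error 0.01, 80% power and 15% drop-out; N = 120 with SD 1.5 (HU and/or gout) and N = 60 with SD 1.0 (neither). The SDs are read here as SDs of change, which the protocol does not say. Drift sizes are assumptions, because the protocol gives no figure for untreated change.

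**The plan's own figure.** For a one-sample t-test on change, power = P(T > t(0.99; n−1)), where T is noncentral t with n−1 degrees of freedom and noncentrality √n × 0.5/SD.
- SD 1.5: 94 evaluable, and 94/0.85 gives 111 enrolled, against 120 stated.
- SD 1.0: 43 evaluable, and 43/0.85 gives 51 enrolled, against 60 stated.

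The stated numbers are not reproduced, but both exceed what the inputs require. After 15% loss, 120 × 0.85 = 102 and 60 × 0.85 = 51 remain, with power of 84% and 87%. That mismatch is conservative and does not bear on this point.

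**Fall needed for significance.** Critical mean fall = t(0.99; n−1) × SD/√n.
- n = 102, SD 1.5: 2.364 × 1.5/√102 = 0.35 mg/dL.
- n = 51, SD 1.0: 2.403 × 1.0/√51 = 0.34 mg/dL.

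**Chance of significance with no drug effect.** Same formula, with the assumed drift d in place of 0.5. Example: n = 51, SD 1.0, d = 0.2 gives noncentrality √51 × 0.2/1.0 = 1.43 and probability 17.5%.

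| Assumed drift (mg/dL) | No HU/gout: n = 51, SD 1.0 | HU/gout pooled: n = 102, SD 1.5 | One HU/gout group: n = 51, SD 1.5 |
|---|---|---|---|
| 0.1 upward | 0.1% | 0.1% | 0.3% |
| 0 | 1.0% | 1.0% | 1.0% |
| 0.1 downward | 5.1% | 4.8% | 3.1% |
| 0.2 downward | 17.5% | 15.9% | 8.1% |
| 0.3 downward | 40% | 37% | 17.5% |
| 0.5 downward | 87% | 84% | 50% |

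The last column is one of the two HU/gout analysis groups in Section 5.1 (about 60 enrolled, 51 after 15% loss). Section 15.2 powers only the pooled 120. The bottom row repeats the design power, as it must: an untreated fall equal to the planned effect passes as often as the planned effect would.

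**Source of the 0.5 mg/dL.** Write the mean fall from baseline on vitamin C as F, the untreated fall as U and the placebo-compared effect as E. Then F = E + U. Section 15.2 sets F = 0.5, while the Background describes the cited source as giving E. F = E requires U = 0, which no section states.

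**The case against.** A single-arm, open-label design is a legitimate choice and is openly declared; Section 12.3 even calls the study a pilot. That stands, and it is why the point concerns the claim and not the design.

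A reader might infer that any small drift would pass as efficacy. The figures do not support that: an observed fall of about 0.34 to 0.35 mg/dL is needed in the powered populations, a true drift of 0.1 is significant only about 5% of the time, and upward drift makes the test conservative.

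A reader might also infer that the study's procedures push urate down in all three groups. The protocol does not show this. Trigger-food questions concern gout flares, so they hardly apply to people without gout. Section 4.1 continues prescribed medicines and Section 8.1 refers to stable ULT. The calls concern safety, tolerance, medication changes and dose timing, and better adherence to vitamin C is exposure to the drug. Dietary history reaches everyone, but no dietary advice is described. Grouping on baseline urate in Section 8.1 is a separate route to non-drug change and is not counted here.

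Section 15.3 adjusts for concomitant medications, which bears on medication change but cannot remove a drift common to all participants.

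Finally, the protocol does not print the 0.5 mg/dL with its comparator, and a meta-analysis of randomized trials could also report within-arm changes. So the mismatch rests on the Background's description and the reference title. That is enough to require reconciliation, not to prove the figure wrong.

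**Conclusion.** The point holds as a mismatch between claim and test. Objective 1 and Ho1 are causal, nobody is untreated, and the only planned test of the urate effect is change from baseline, so the 0.01 level does not apply to a statement about vitamin C. Under assumed downward drifts of 0.1 to 0.3 mg/dL and no drug effect, the error rate for that statement would run from about 5% to 37–40% in the two powered populations, and from about 3% to 17% in a single HU/gout group. An upward drift of 0.1 would bring it to about 0.1% in the powered populations. These figures rest on assumed drifts and on reading the Section 15.2 SDs as SDs of change. They illustrate sensitivity and do not estimate what will happen. The documents do not show that urate will drift, or in which direction; they show that the plan could not tell drift from drug effect.

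**What to change.** 1. Reword Objective 1 and Ho1 as change in serum urate, gout symptoms and BMI during 8 weeks of vitamin C.
2. In Section 15.2, reconcile the 0.5 mg/dL with the Background: state that it comes from placebo-compared trials and that using it as a fall from baseline assumes no untreated change.
3. In Section 15.2, state that the one-sided 0.01 level refers to change from baseline, and that this test alone will not support attribution to vitamin C.

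The cost is a weaker claim, with no new participants or data. Optionally, repeat the analysis in participants with no ULT or other medication change between visits; medication history is taken at both. This addresses medication drift only, and the rewording carries the correction.

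A concurrent control would support the causal claim but is out of proportion here. By the two-sample normal formula, n per arm = 2 × [SD × (2.326 + 0.842)/0.5]². With SD 1.5 this is 181 evaluable, 213 enrolled per arm and 426 in total; with SD 1.0 it is 81, 96 and 192. Together that is 618, against the planned 180.

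### Section 15.2 powers Ho1 for one pooled HU/gout sample of 120, but sections 2.0 and 5.1 plan the analysis in ULT strata of about 60, each with roughly 50% power

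*Protocol*

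**What the plan says.** Section 15.2 gives the only power statement. It begins "For an effect size of 0.5 mg/dL SU reduction from baseline by vitamin C", "using a one-sided *t*-test", with "80% power, type 1 error of 0.01, and 15% drop-out rate". It concludes that two samples are required: "120 in adults with HU and/or gout (standard deviation, SD of 1.5 mg/dL") and "60 adults without HU and gout (SD of 1 mg/dL"). These match the two populations that Ho1 names in section 2.0, healthy adults (a) and patients with HU and/or gout (b).

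The text under Ho1 in section 2.0 then describes a different analysis. To test parts (a) and (b), the investigators will "analyze by 3 groups: 1) participants with HU and/or gout with ULT, 2) participants with HU and/or gout without ULT", and the third group is participants with neither condition. Section 5.1 sets the sizes: "We aim to have 3 analysis groups of about 60 people per group (total about 180 participants").

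Section 15.3 describes an adjusted linear regression for serum urate change and mentions neither a pooled nor a three-group comparison. No section gives power for either HU/gout group of 60.

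**The concern.** The protocol states both the analysis groups and the power, and the two do not correspond. The larger SD assumed for HU/gout is the reason that population needs the larger sample. Once it is divided by ULT, each half has the size planned for the non-HU group but keeps the larger SD.

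Serum urate change is the primary endpoint, and the ULT split is where readers will look to see whether vitamin C adds anything with or without ULT. With power near one half, a non-significant stratum is about as likely as a significant one even if the assumed effect is real. A reader who takes 80% as the power of each planned group analysis could read that result as no effect. If one stratum is significant and the other is not, it could be mistaken for a difference in response by ULT.

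**Working it through.** **Inputs, all from section 15.2 except the group sizes.** Mean fall δ = 0.5 mg/dL; one-sided α = 0.01; target power 80%; drop-out 15%; SD 1.5 (HU/gout) and 1.0 (no HU or gout). Section 5.1 gives about 60 per analysis group. The test is taken as a one-sample t-test on change from baseline. A two-sample test would need 181 per arm at SD 1.5, so it cannot be the basis.

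**Step 1: the protocol's own figures.** Normal approximation: n = (SD × (z₀.₉₉ + z₀.₈₀)/δ)², with z₀.₉₉ + z₀.₈₀ = 2.326 + 0.842 = 3.168.
- SD 1.5: (1.5 × 3.168/0.5)² = 90.3, so 91 evaluable; 91/0.85 gives 108 enrolled. Exact noncentral t: 94 evaluable, 94/0.85 gives 111 enrolled.
- SD 1.0: (1.0 × 3.168/0.5)² = 40.1, so 41 evaluable and 49 enrolled. Exact t: 43 evaluable, 51 enrolled.

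The stated 120 and 60 are not reproduced exactly, and none of the variants tried (one- or two-sided, normal or t, either drop-out inflation) gives both. Against the one-sided calculation that section 15.2 describes, they err on the large side, so at least 80% power for those two samples is confirmed.

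**Step 2: power at the planned sizes.** Completers: 120 × 0.85 = 102; 60 × 0.85 = 51. Power is the probability that a noncentral t with n − 1 degrees of freedom and noncentrality δ√n/SD exceeds the one-sided 1% critical value.

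| Test | Completers | SD | Noncentrality | Power |
|---|---|---|---|---|
| HU/gout pooled | 102 | 1.5 | 0.5 × √102/1.5 = 3.37 | 84.0% |
| No HU or gout | 51 | 1.0 | 0.5 × √51/1.0 = 3.57 | 87.4% |
| Each HU/gout stratum | 51 | 1.5 | 0.5 × √51/1.5 = 2.38 | 49.6% |

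Check on the last row by normal approximation: 2.38 − 2.326 = 0.054, giving 52.2%. With no drop-out (60 completers), the exact figure is 57.8%.

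**Step 3: sensitivity to the within-stratum SD (51 completers, δ = 0.5).**

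| SD | 1.0 | 1.2 | 1.5 | 1.8 |
|---|---|---|---|---|
| Power | 87% | 72% | 50% | 35% |

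**Step 4: detectable fall.** At 51 completers and SD 1.5, 80% power requires a mean fall of 0.68 mg/dL (exact t). Equivalently, 0.5 mg/dL is detectable with 80% power only if the SD is about 1.5 × 0.5/0.684 = 1.10.

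**Step 5: what 80% per stratum would take.** 111 enrolled in each HU/gout stratum, 2 × 111 = 222 in place of 120.

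**The case against.** The strongest reply is that section 15.2 matches the hypothesis as written. Ho1 names two populations, section 15.2 sizes exactly those two, and section 5.1 describes 2:1 enrolment between them. Analysis by three groups could mean stratified reporting, and the regression in section 15.3 adjusts for concomitant medications, which may include ULT. This largely stands: the calculation is adequate for the two samples it covers. It does not settle the matter, because section 2.0 says that Ho1 (a) and (b) will be tested by the three-group analysis, and no section names the pooled test as the primary one.

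A second reply is that 50% is conditional. The protocol gives SD 1.5 for HU/gout as a whole and does not say whether it is the SD of change. The SD within a ULT stratum may differ, and covariate adjustment may add precision. This stands too, which is why a range is given.

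Three stronger readings are tempting but not supported:
- A reader might infer that section 15.2 contains an arithmetic error, or that the statement in section 5.2 about 180 participants reaching statistical power is untrue. No passage claims 80% power for a ULT stratum, and 180 is simply 120 + 60.
- A reader might ask for the chance that both strata are significant. No passage requires that.
- A reader might infer that ULT users will not respond, because section 2.0 cites a trial that "did not find significant serum urate reduction in patients on allopurinol". That trial used 500 mg once daily rather than twice daily, and a non-significant result does not establish zero effect. A reduced response in ULT users may be examined only as a labelled assumption.

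**Conclusion.** The point holds as a mismatch between the powered analysis and the planned one. Under the section 15.2 assumptions, the pooled HU/gout test (about 84%) and the non-HU test (about 87%) meet the 80% target. Each ULT stratum of about 60 has about 50%, with a detectable fall of about 0.68 mg/dL rather than 0.5.

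The stratum figure rests on two assumptions that the protocol does not state by stratum: a 0.5 mg/dL fall and an SD of 1.5 within each. It is 58% with no drop-out and runs from 35% to 87% for an SD of 1.8 down to 1.0. This is an inconsistency that should be fixed; it does not undermine the sample size for the pooled test.

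**What to change.** Reconcile sections 2.0, 5.1 and 15.2:

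1. In section 15.2, name the pooled HU/gout test (120 enrolled) and the non-HU test (60 enrolled) as the powered Ho1 tests.
2. In sections 2.0 and 5.1, describe the ULT and non-ULT strata as estimates with confidence intervals.
3. In section 15.2, state that each stratum has about 50% power under the stated assumptions, give the range by SD and the detectable fall of about 0.68 mg/dL, and say that a non-significant stratum is not to be read as no effect.
4. If a reduced response in ULT users is explored, label it as an assumption.

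If the three-group tests are meant to be primary, replace 80% with about 50%/50%/87% (HU/gout with ULT, HU/gout without ULT, neither condition) under those same assumptions.

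The cost is wording in three sections. No participants are added and no procedure changes; the stated power for the ULT strata simply becomes less favourable.
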